# Exercise interveNtion outdoor proJect in the cOmmunitY—ENJOY program for independence in dementia: a feasibility pilot randomised controlled trial study protocol

**DOI:** 10.1186/s40814-022-01027-x

**Published:** 2022-03-22

**Keywords:** Dementia, Cognitive decline, Physical activity, Falls, Built environment, Age-friendly, Seniors Exercise Park

## Abstract

**Background:**

While the underlying neuropathology of dementia is not curable, interventions and treatment, such as physical activity, can offer physical and functional gains leading to better mobility, independence and quality of life. The Seniors Exercise Park program is an evidence-based physical and social activity program using an innovative design in outdoor exercise equipment specifically designed for older people. This unique program has never been tested with older people living with dementia. This study will evaluate the feasibility of delivering the Seniors Exercise Park program for people living with mild to moderate dementia in residential aged-care. This study will identify the optimal physical activity program, evaluate the safety of equipment usage and determine optimal supervision needs. The potential physical, social, quality of life and cognitive benefits of participation in the Seniors Exercise Park program will also be examined.

**Methods:**

This is a feasibility pilot randomised controlled design with pre-post evaluation. Adults aged ≥ 60 years who have symptoms of dementia and/or who have been diagnosed with dementia will be recruited from an aged-care facility in Melbourne. Participants allocated to the intervention group will undergo a 12-week structured supervised physical activity program using the outdoor Seniors Exercise Park equipment followed by a 12-week maintenance phase (unstructured physical activity). Participants will be assessed at baseline, 3 and 6 months. Participants allocated to the control group will attend activities provided by the aged-care facility. A sample of 12 participants per group is the targeted sample size. Feasibility will be evaluated in terms of recruitment rate, retention, attendance, overall adherence, dropout rate, adverse events, modifications to the exercise program delivery and supervision needs. A comprehensive suite of cognitive and health-related questionnaires and physical function measures will also be collected.

**Discussion:**

The ENJOY program for independence in dementia will determine the suitability of the Seniors Exercise Park program for people diagnosed with mild to moderate dementia. Outcomes could inform future design of dementia-friendly built environments to increase physical activity participation for residential aged-care facilities.

**Trial registration:**

This trial is registered with the Australian New Zealand Clinical Trials Registry—Registry Number ACTRN12620000733976. Registered on the 13th of July 2020.

## Introduction

The world’s population is ageing rapidly, with the number of people aged over 65 years doubling to around 25% of the total population over the next 40 years. The number of Australians aged 65 and over is expected to increase from around 2.5 million in 2002 to 6.2 million in 2042 [1]. An estimated 459,000 Australians had dementia in 2020 [2], 99% of whom were aged 60 and over [3]. The total number of people affected by dementia is projected to rise to 900,000 by 2050. In Australia in 2015, almost half (49%) of people living in residential aged-care had a diagnosis of dementia and nearly all had an associated disability [3].

Participation in physical and social activities as part of quality dementia care is crucial for optimising the health and independence for people living in aged-care facilities. There are no disease-modifying treatments for dementia, so interventions that assist in the management of symptoms, such as physical activity, can offer physical and functional gains leading to better mobility, independence and quality of life. Physical activity offers many health benefits for older people, including improvement in cognitive function [4]. Less than 25% of older Australians do enough physical activity to achieve health benefit, and those living in residential aged-care spend the majority of their time inactive with lengthy periods of sedentary behavior [5, 6]. Furthermore, many have one or more functional dependencies and require assistance with daily living activities or ambulation. Exercise and physical activity programs that target daily life mobility-specific activities (e.g. sit to stand, transfer movements), have been shown to be effective in improving mobility limitations in older people living with dementia [7]. Novel enjoyable exercise programs that can motivate people living with dementia in aged-care facilities to engage regularly in physical activity are needed.

Being outdoors provides important benefits for older people [8, 9]. People living with dementia also showed benefits from being outdoor as it provides both physical and psychological health benefits as well as calming effect [10–12]. It may also improve cognition [13]. Encouraging older people to spend time outdoors might be effective in preventing cognitive decline among those with limited physical function, as going outdoors less than once a week was associated with cognitive decline among older adults with limited physical function [14]. Combining physical activity in outdoors environments might have added benefits for people living with dementia.

The Seniors Exercise Park is an innovative design in outdoor exercise equipment, integrating multiple exercise stations specifically designed for older people. This unique outdoor equipment offers a fun but physically challenging environment to support exercise and to challenge key aspects of physical health for older people, including balance (e.g. unstable walking bridge, narrow walking beam), mobility (e.g. shoulder range of movement), strength and function (e.g., sit to stand, stairs) [15]. In our previous randomised controlled trial, we tested the feasibility and effectiveness of using the Seniors Exercise Park as part of a physical activity and social support program (the Seniors Exercise Park program) for older people (without dementia or cognitive impairment). This research has provided the initial evidence demonstrating the physical and social benefits of the Seniors Exercise Park program for older people [16, 17]. Furthermore, in order to investigate its potential wider usage and health benefits in the community, a large community research project was undertaken 2018–2020 (the ENJOY project, 95 participants recruited). The ENJOY project involved the installation of the specialised outdoor equipment at public spaces and in an aged-care setting, together with the delivery of the evidence-based physical and social activity program for older people. The results from the ENJOY project further demonstrated the positive impact of the social and physical activity program on sustained engagement in physical activity and wellbeing and highlighted this novel approach as an important public health infrastructure investment in promoting physical activity for older people without cognitive impairment [18, 19].

Despite the positive health benefits reported, this innovative outdoor physical activity and social program has never been tested on and applied to people living with dementia. Therefore, the ENJOY program for independence in dementia aims to design, deliver and test this program in older people living with dementia in a residential aged-care. The optimal physical activity program, its safety and supervision needs will be examined to determine its suitability for people diagnosed with mild to moderate stage dementia. In addition, the physical, social, health and cognitive benefits of participation in the Seniors Exercise Park program will also be examined.

## Method and design

All procedures involved in this trial will be conducted in compliance with the National Statement on Ethical Human Research and the Australian Code for the Responsible Conduct of Research. Ethical approval has been obtained from the Melbourne Health Ethics Committee, Melbourne, Australia (HREC/61926/MH-2020). The study was designed according to the Consolidated Standard of Reporting Trials (CONSORT) guidelines and publications associated with the trial will be reported according the CONSORT 2010 Statement [20, 21].

### Design and setting

This study is a feasibility pilot randomised controlled trial with pre-post evaluation. Older people aged 60 years and over who reside in Leith Park aged-care facility in Melbourne and who experience symptoms of dementia (such as memory loss or forgetfulness) consistent with a diagnosis of dementia and/or have a formal diagnosis of dementia will be recruited. Participants will be randomised to either an exercise intervention group (Seniors Exercise Park program) or to a control group. Participants from the intervention group will undergo a 12-week supervised structured physical activity program using the Seniors Exercise Park outdoor equipment, followed by a 12-week maintenance phase (unstructured independent exercise). Participants from the control group will be given the opportunity to participate in organised recreation and leisure-based group activities such as art and music (as part of the aged-care facility’s standard care). All participants will be assessed at baseline, 3 months and 6 months follow-up as detailed in Fig. 1.

**Fig. 1 Fig1:**
[figure not shown]
Chart flow of the ENJOY program for independence in dementia project’s design

### Study population

#### Inclusion criteria

Older people from the Leith Park aged-care facility will be recruited if they meet the following inclusion criteria: (1) aged 60 years or older and reside at the aged-care facility; (2) have been diagnosed with mild to moderate dementia, OR suspected to have dementia by the aged-care staff and a screening test score of Standardised Mini-Mental State Examination (sMMSE > 10), OR have cognitive problems that, in the opinion of the experienced staff, puts them in the cognitively impaired domain with suspected mild to moderate dementia, and a screening test score of sMMSE > 10 [22]; (3) are able to stand by themselves with or/without hand support; (4) are able to walk without manual (physical) assistance from staff and; (5) are able to follow simple exercise instructions.

#### Exclusion criteria

Older adults will be excluded from this study as follows: (1) participants who are unable to stand by themselves with or without hand support; (2) unable to walk without manual (physical) assistance from staff (with or without walking aid); (3) unable to comprehend simple instructions during the exercise program (this exclusion criterion will be determined by the intervention health professional within the first two classes, based on their observation of each participant in the first two sessions); (4) have severe dementia (score on the sMMSE ≤ 10) [22]; (5) score on the sMMSE > 24 (6) participants with other terminal or unstable illness or chronic conditions, or any documented medical condition or physical impairment that is deemed by their medical practitioner to contraindicate their inclusion.

### Recruitment and consent process

Information about the study will be provided to residents and their family members by the aged-care staff via verbal communication, flyers placed at reception and letters sent to family. Potential participants (who have been diagnosed with dementia or suspected to have dementia) will also be identified by the aged-care staff. This will be done based on their knowledge of the resident and the resident’s medical record file. Those who are diagnosed or suspected to have mild to moderate dementia (with a sMMSE score of > 10) will be given information about the study. Details of potentially eligible and interested participants will be provided to the research staff, who will then follow up with a phone call (to the family member/nominated representative) or in-person via a visit at the aged-care facility to further ascertain the resident’s interest to participate, and their capacity to consent. During that visit, the researchers will provide the resident with the information sheet. If it is deemed that the participant has the capacity to consent, an appointment will be made for the baseline testing. If it is determined that the resident does not have capacity to consent, but could participate in some or all parts of the project (able to answer questionnaires and follow exercise instructions), the research team will contact the nominated representative of the resident (as defined by the legislation in the relevant jurisdiction). The nominated representative will be asked to sign a consent form along with assent from the resident.

### Randomisation

Randomisation (1:1 basis) will take place after completion of the baseline testing. Participants will be randomly allocated to one of the following groups: (1) control group or (2) Seniors Exercise Park program group. Randomisation will be stratified by dementia severity (moderate or mild) based on the Standardised Mini-Mental State Examination (moderate sMMSE > 10 but < 20; mild sMMSE ≥ 20 but ≤ 24) [22]. Block randomisation will be undertaken using opaque envelopes, so that blocks of 6–8 participants (3–4 for intervention group and 3–4 for control group) will be randomised at a time. It is expected that recruitment will be undertaken over a period of 6–10 months to achieve a target sample size of 12 participants in each group. Assessors and participants will not be blinded to their respective group allocation. While there are clear benefits from a research perspective to blind assessors, having the same staff undertake assessments and interventions may reduce confusion and improve relationships for the person with dementia where a minimum number of research staff are involved.

### Procedure

At the baseline assessment, the following information will be recorded via semi-structured interview with the participant: demographic characteristics (age, gender), anthropometric measures (height and weight), previous medical history, current medication usage, socioeconomic and cultural background information (e.g. employment, level of education, country of birth, years of residency in Australia) and falls history (number of falls in the past 12 months). Information about medical history, medication usage, dementia diagnosis and falls history will also be extracted from the participant’s medical record kept onsite, to cross-check and to optimise accurate data collection.

At baseline, 3 months and 6 months participants will undergo a comprehensive suite of physical function (strength, balance, functional mobility) tests, psychosocial (quality of life, loneliness, depression) questionnaires, falls risk assessment and falls history assessments. Randomisation will take place at the completion of the baseline assessment. Those who are randomised to the exercise intervention group will be required to obtain a medical clearance from the General Practitioner on-site prior to commencing participation in the exercise program. Study design and study procedures and assessments are provided in Fig. 1 and Table 1 respectively.

**Table 1 Tab1:**
[figure not shown]
Study schedule

The assessments at baseline, 3 months and 6 months will take approximately 1–1.5 h and be conducted at a room at the Leith Park aged-care facility (Liscombe House). Participants will be given as many breaks as needed during the assessment and will also be able to complete it in two visits if requested and/or the resident reports fatigue.

### Assessments

#### Primary outcome

The primary outcomes for this study are the feasibility, safety and supervisory needs associated with the program:

##### Feasibility

Feasibility of the program will be determined based on the following: recruitment (% approached who agreed to participate), completion of the intervention (retention), attendance, overall adherence, dropout rate, adverse events (falls, muscle/joint pain), any modification in the exercise program delivery (optimisation of program structure) and supervision needs. Adherence to exercise interventions in people with dementia in the aged-care setting varies from 25.5 to 84% with high variability between studies [23]. Our previous study showed 80–86% adherence to the Seniors Exercise Park exercise program [17, 19]; however, we anticipate some potential barriers for participation (e.g. mental wellbeing, anxiety, depression, decreased mobility) as reported for people living with dementia [23]. We are aiming for an estimated participation rate of ≥ 70% of the prescribed number of exercise sessions [24] during the 12-week structured exercise program, and ≥ 60% adherence for the overall 6-month exercise program. Retention of 85% of the sample is expected (with estimate 15% drop out) at 6 months.

##### Safety

Safety will be assessed based on the following: any falls that occur during the exercise delivery sessions, any adverse events (joint/muscle pain during the exercise, or as a result of the exercise sessions), serious adverse events (any report of difficulty breathing that does not settle quickly with rest, new or unrelenting chest pain, or acute changes in the level of consciousness during the session where a medical emergency procedure is required). Any incidents and or events will be recorded at each session.

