##### Falls

Any falls occurring during the exercise sessions will be recorded. A fall is defined as an event when the participant ‘inadvertently comes to rest on the ground, floor or other lower level’ (WHO Global Report on Falls Prevention in Older Age [44]).

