##### Cardiorespiratory adverse reaction

Any report of difficulty breathing that does not settle quickly with rest, new or unrelenting chest pain, or acute changes in the level of consciousness during the session, may precede a serious medical emergency. A potentially serious event will be defined if the participant reported difficulty breathing but symptoms settled quickly with rest and their clinical signs (respiration rate, heart rate, oxygen saturation) remain normal. A serious adverse event will be defined if symptoms have not settled and medical emergency care was required.

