### Statistical analysis

Data for the feasibility and safety components of the study will be analysed as follows (mean, standard deviation and proportion): proportion of participants approached to participate who did commence the program, percentage of participants who complete the intervention, overall percentage of sessions attended, number of participants who dropout, any falls that occur during the exercise sessions, any muscle/joint pain during or after the exercise sessions, and serious adverse events requiring medical attention. Modifications of the exercise program will be reported and a recommended refined structure will be presented at the end of the program.

An acceptable level for feasibility of the program will be based on the following: ≥ 70% adherence of the prescribed number of exercise sessions [24] at the 12-week structured exercise program completion, and a ≥ 60% adherence for the overall 6-month exercise program, with retention of 85% of the sample (estimate 15% drop out).

To determine statistical trends of effectiveness, analyses of the selected outcomes such as cognitive, physical function, quality of life and social measures will be performed to assess the changes within and between groups over time (pre/post). Repeated measures ANOVA with factors of intervention (Seniors Exercise Park program, control) and time (pre-post intervention and follow-up) will be used. A post hoc analysis will be undertaken using the group differences and variability within groups on the secondary measures to determine the required sample size for a future adequately powered study using these outcomes.

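### The serious-event definition covers only cardiorespiratory and consciousness symptoms in a session, so a session-related fall with a fracture, admission or death can stay out of the serious-event count

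*Protocol article*

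**What the plan says.** The Primary outcome section states: "The primary outcomes for this study are the feasibility, safety and supervisory needs associated with the program".

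The Safety section then sorts harms into three classes:

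- Falls: "any falls that occur during the exercise delivery sessions".
- Adverse events: "any adverse events (joint/muscle pain during the exercise, or as a result of the exercise sessions".
- Serious adverse events: "serious adverse events (any report of difficulty breathing that does not settle quickly with rest, new or unrelenting chest pain", continuing "or acute changes in the level of consciousness during the session where a medical emergency procedure is required".

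It adds that incidents are recorded at every session.

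Under Cardiorespiratory adverse reaction, the article returns to the same three symptoms and says: "A serious adverse event will be defined if symptoms have not settled and medical emergency care was required". Under Falls it gives a definition of a fall and says: "Any falls occurring during the exercise sessions will be recorded". It attaches no rule on when a fall is serious.

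The Statistical analysis section reports falls in sessions, muscle or joint pain, and "serious adverse events requiring medical attention" as separate items.

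**The concern.** The intervention puts residents with dementia on balance and stair equipment. A fall with injury is a foreseeable serious harm of such a programme, and it is the one that the serious-event wording does not reach. If staff follow the text, a resident who falls and is unharmed and a resident who falls and breaks a hip both appear as one fall, and neither appears as a serious event. A cardiac event that starts soon after a session has a similar problem, because the serious-event list is tied to the session.

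What is at stake is the meaning of one reported figure. Safety is a primary outcome, the Discussion says that a successful result would represent a safe programme, and the Sample size section looks ahead to a large multi-site trial. A statement that no serious adverse events occurred would be read by most readers as covering fractures and admissions. Under the stated definition it would not.

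**Working it through.** **1. The plan's own figure.** The Sample size section gives 12 per group, 24 in total, and 20 completing after about 15% dropout. Check: 20 / (1 − 0.15) = 23.5, rounded up to 24; forward, 24 × 0.85 = 20.4. The figure reproduces, and 12 is the denominator used below. The article states no expected serious-event rate and no safety threshold.

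**2. The definitions side by side.**

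| Section | What makes an event serious | Care condition |
|---|---|---|
| Safety | Unsettled breathing difficulty, new or unrelenting chest pain, acute change in consciousness, in the session | Medical emergency procedure |
| Cardiorespiratory adverse reaction | Same symptoms, not settled | Medical emergency care |
| Falls | No criterion | None |
| Statistical analysis | Not redefined | Medical attention |

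The three care conditions differ. Medical attention is the widest, but it qualifies serious adverse events and does not say which events those are.

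**3. Applying the text to example events.**

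| Event | Falls line | Serious-event line |
|---|---|---|
| Fall in session, unharmed | Yes | No |
| Fall in session, hip fracture and admission, alert throughout | Yes | No |
| Fall in session, altered consciousness, emergency procedure | Yes | Yes, through the consciousness criterion |
| Unsettled chest pain in session, emergency care | No | Yes |
| Chest pain starting soon after a session | No | No |

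The last row reads the session limit as governing the whole list. If it attaches only to the change in consciousness, that row becomes uncertain. The fracture row does not change on either reading.

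**4. Size.** One misclassified event in the exercise arm is 1/12 = 8.3%, while the serious-event line reads 0/12. The one-sided 95% upper limit for 0/12 is 1 − 0.05^(1/12) = 22.1%. That limit comes from n = 12 under any definition. It shows how little a zero would say, not how large the misclassification is.

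**5. How likely is it to matter?** The article gives no rate, so this is an assumption. Let p be a participant's risk of a session-related serious injury or admission outside the listed symptoms. The chance of at least one among 12 is 1 − (1 − p)^12:

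- p = 2%: 21.5%
- p = 5%: 46.0%
- p = 10%: 71.8%

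**6. Time window.** Two sessions of 1 to 1.5 h a week are 2 to 3 h out of 168 h, or 1.2% to 1.8% of the week. For muscle and joint pain the plan already counts what results from a session as well as what happens in it. For serious events it does not.

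**The case against.** The strongest case on the other side is that the lists in brackets are loose. The Feasibility section puts falls among adverse events, while the Safety section lists them apart. The second serious-event sentence sits under a cardiorespiratory heading and may serve only that category. The analysis wording has no organ-system limit, so a fracture could be said to fit it. This shows that the sections need reconciling. It does not supply a criterion for injury, because no section names one.

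Several stronger readings are tempting, and the article does not support them:

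- A reader might infer that an injurious fall or a death can never be a serious event. It can, if it comes with one of the listed symptoms in the session and the emergency condition is met. It then counts because of the symptom.
- A reader might infer that the harm would go unreported. It would not: falls in sessions have their own reporting line, incidents are recorded at each session, research staff complete post-session notes, and falls history is assessed at 3 and 6 months. The risk is misclassification.
- A reader might infer that falls are recorded only as present or absent. The article does not say what the incident form holds, and an article may leave that to the full protocol.
- A reader might infer that a decision turns on the count. The acceptability criteria are adherence (70% and 60%) and retention (85%). None uses serious events.
- A reader might infer that all admissions in both arms must be counted to 24 weeks. The control group has no exercise sessions and so can have no serious event under this wording. But the outcome is safety associated with the programme, so session-based capture is a coherent choice. With 12 per arm, a comparison of background admissions would say little.

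**Conclusion.** The concern holds in a limited form. As written, a session-related fracture, admission or death without the listed symptoms is reported as a fall, or as an unclassified incident, and does not enter the serious-event count of a primary outcome. The three sections that describe serious events also use three different care conditions. One such event would be 8.3% of the exercise arm, shown as 0/12 on the serious-event line.

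This rests on taking the Safety list as the definition, which is the natural reading because the article offers no wider one. The part about cardiac events after a session also assumes that the session limit applies to the whole list. The likelihoods in the working depend on assumed risks.

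I rate this as should-fix. It is a real defect in how a primary outcome is defined, but the raw event is still recorded and no feasibility threshold depends on the count.

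**What to change.** Use one outcome-based reporting definition in the Safety, Cardiorespiratory adverse reaction and Statistical analysis sections. A serious adverse event would be death, hospital admission or transfer, fracture or other injury needing medical treatment, or emergency care, occurring during a session or as a result of one. Keep the breathing, chest pain and consciousness signs as examples. For each fall, report whether it caused injury and what the outcome was. This changes how events are counted and reported. It does not change the exercise programme, the handling of any event or the sample size.

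The cost is small: wording in three sections and, where the incident form does not already hold it, a field for injury and outcome. The serious-event count may be higher. Someone must also judge whether a later event resulted from a session, and the staff are not blinded, so the basis for that judgement should be noted with each event.

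Capturing serious events over the whole follow-up in both arms is optional. The article describes extraction from the on-site medical record at baseline only, so reviews at 3 and 6 months would be new work, and background admissions in this population would add to the count in both arms.
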